##### General Parenting Practices

Existing scales are also employed to measure parent practices addressed as part of the intervention, including: (1) the Alabama Parenting Questionnaire - Preschool Revision (APQ-PR), which includes subscales for positive parenting, inconsistent parenting, and punitive parenting [26]; (2) the Difficulties in Emotion Regulation Scale (DERS), which assesses parent ability to manage their own emotional responses and includes subscales for non-acceptance of emotional responses, difficulties engaging in goal-directed behavior, impulse control difficulties, lack of emotional awareness, limited access to emotion regulation strategies, and lack of emotional clarity [27]; (3) the Coping with Children's Negative Emotions Scale (CCNES), which assesses how parents react to children's negative affect in distressful situations and includes subscales for distress reactions, punitive reactions, expressive encouragement, emotion-focused reactions, problem-focused reactions, and minimization reactions [28,29]; (4) the Confusion, Hubbub, and Order Scale (CHAOS), which assesses parental time management skills (e.g., use of routines) [30]; and (5) the Parenting Convergence Scale (PCS), which assesses the degree to which parents work together to tackle parenting responsibilities and includes subscales for communication, conflict, and support [31,32].

##### Parent Feeding Practices

Parent feeding style and behaviors are assessed using a combination of items from existing instruments including: (1) the Caregiver's Feeding Style Questionnaire (CFSQ), which assesses two dimensions of parent feeding - demandingness and responsiveness) [33]; (2) the Parental Feeding Style Questionnaire (PFSQ), which includes subscales for emotional feeding, instrumental feeding, prompting/encouragement to eat, and control over eating [34]; and (3) nine subscales from the Comprehensive Feeding Practices Questionnaire (CFPQ), specifically those for child control, child involvement, parent modeling of healthy eating, parent monitoring of child intake, parental pressure to eat, parent restriction for health, parent restriction for weight control, encouraging of balance and variety, and teaching about nutrition [35].

##### Parent Physical Activity-Related Practices

Measures of parent practices specific to physical activity are not well developed; therefore, a tool was developed by investigators based on an extensive literature review (unpublished data) and using items and scales taken or modified from existing instruments [36]. Items assess constructs such as indoor/outdoor rules, use of physical activity as a reward or punishment, monitoring, control, support, parent role-modeling, family activity, praise, encouragement, education, and use of screen time for distraction.

##### Parent Motivation to Change Practices

Given the inclusion of the Self-Determination Theory Framework in our conceptual model, measures of intrinsic/autonomous motivation to change behavior are also assessed. Autonomous motivation to change is assessed with the Treatment Self-Regulation Questionnaires (TSRQ), which measures controlling vs. autonomous reasons an individual has for adopting certain healthy behaviors [37]. The original measure was modified for this study to ask parents why they would adopt more positive parenting practices. Parents' feelings of competence are assessed using three separate measures: one focusing on feelings of competency related to their role as a parent, and the last two focusing on feelings of competency specific to helping their child meet dietary and physical activity recommendations. Additional measures include the Parenting Sense of Confidence (PSOC) scale, which assesses parents' self-efficacy (competence, problem-solving ability, and capability) and satisfaction (affective dimension reflecting frustration, anxiety, and motivation) related to their role as a parent [38]; as well as the Parenting Self-Efficacy for Children's Healthy Weight Behaviors (PSE-CHWB), an instrument developed by investigators to assess parents' self-efficacy for adopting parenting behaviors that will help their children meet dietary and physical activity guidelines and promote healthy weight gain. Additionally, parent feelings of relatedness (i.e., attachment, social integration, reassurance of worth, reliable alliance, guidance, and opportunity for nurturance) are assessed using a modified version of the Social Provisions Scale (SPS) [39,40]. Items were adapted for this study to ask specifically about social support for general parenting.

##### Other variables

Several other variables thought to be related to the primary constructs of interest are assessed, including parenting stress (Parenting Stress Index [41]), parent depressive symptoms (Center for Epidemiologic Studies Depression Scale [42]), and child behavior (Eyberg's Child Behavior Inventory [43]), but will not be described in detail in this paper.

### Evaluation

Descriptive statistics will be used to compare the demographic characteristics of intervention and control arm participants at baseline - medians for continuous variables and proportions for categorical variables. All statistical tests and exploratory and confirmatory factor analyses on the physical and parenting and child psychological measures will be performed with either SAS 9.2 (SAS Institute, Cary NC) and MPlus [44]. Statistical tests will be conducted using a two-tailed test with an alpha value set at 0.05. Intervention implementation will be described using process evaluation data based on Glasgow's RE-AIM framework [45] and Kirkpatrick's Training Evaluation Model [46].

An intention-to-treat approach will be used for the primary hypothesis: the comparison of the mean change difference in child percent body fat from baseline to post-intervention between intervention and control children. We expect that our intervention will be effective in producing an absolute difference in change in percent body fat of 2%-3% between the two arms at post-intervention (35 weeks), but power was calculated based on the less optimistic 2% and with a conservative two-sided test of significance.

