### Power Calculation

The study is powered on its primary outcome: mean change difference in child percent body fat, estimated from the Dezenberg et al. [17] formula between intervention and control children. The power calculation assumed an absolute change difference in percent body fat of 2% at the 35-week post-intervention point. The power calculation determined that 280 families needed to be recruited and randomized to provide at least 80% power, assuming a two-sided test at the 5% level, and a retention rate of 80% at the post-intervention assessment.

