### Randomization

For each wave, participants are first stratified by income (household income more or less than $50,000) and county. Household income of $50,000 represents the approximate median household income for the counties targeted for recruitment and was therefore selected as the cut point for income stratification. For each wave and county combination, two randomization tables (one for each income level) are created using SAS 9.2 (SAS Institute, Cary NC) with a randomization allocation ratio of 1:1 and a block size of 2 to ensure balance between study arms across all strata. These randomization tables are then used to create sets of sequentially ordered cards that are sealed so that the condition assignment (control vs. intervention) appearing inside is not visible.

Participants have the opportunity to select a card and be randomized upon arrival to a kick-off event. For each wave, three to four kick-off events are offered. At the beginning of each event, cards from each of 2 stacks are placed into either pail "A" or "B", corresponding to income strata. The number of cards in the pail always exceeds the expected number of participants from each income stratum expected to attend the event. Cards in each pail are shuffled and as participants arrive, staff instruct participants to select one card from the appropriate pail. Cards remaining from the first event are left in the pails and used for the next event, with additional cards added as needed. Stratification procedures are not communicated to the participants.

At these kick-off events, families randomized into the intervention group immediately start their first session, while those randomized into the control group have a short child entertainment program (e.g., book reading, puppet show). Participants must complete baseline measures and attend one of these kick-off events in order to be randomized into the intervention or control group, and continue their participation in the study. This creates a run-in period and helps minimize loss to follow-up.

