#### Primary Outcome

The primary outcome is mean change difference in child percent body fat between baseline and post-intervention. Percent body fat is calculated using the formula of Dezenberg et al.[17] which incorporates weight, triceps skinfold, gender, and race/ethnicity. Collection of anthropometric data is described in detail below; sex is captured by the technician during measurement; and race/ethnicity is reported by the parent. The Dezenberg equation has been validated in 4-11 yr old Caucasian and African American children and found to be highly predictive of body fat mass measured by DEXA (R^2 ^= 0.95, Model SEE = 0.50)[17].

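### The primary comparison is defined as a difference in mean change, with no adjustment named for baseline body fat or the randomisation strata; adding it would gain precision at no data cost

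*Protocol article*

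**What the plan says.** Under Primary Outcome the article states: "The primary outcome is mean change difference in child percent body fat between baseline and post-intervention". The Evaluation section repeats this as "the comparison of the mean change difference in child percent body fat from baseline to post-intervention between intervention and control children", to be done by intention to treat. On testing, that section adds: "Statistical tests will be conducted using a two-tailed test with an alpha value set at 0.05". It names the software but no test, model or covariate list. Study Hypotheses and Power Calculation also express the primary question as a difference in change.

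The Randomization section says: "For each wave, participants are first stratified by income (household income more or less than $50,000) and county". Allocation is 1:1 in blocks of 2, from separate tables for each income level within each wave and county. Baseline measures must be completed before a family can be randomised.

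The Power Calculation section states that "280 families needed to be recruited and randomized to provide at least 80% power", "assuming a two-sided test at the 5% level". It gives neither a standard deviation nor a baseline to follow-up correlation.

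**The concern.** The article fixes two design features, a change-from-baseline contrast and a stratified randomisation. No analysis statement then uses the baseline value as a covariate or uses the strata.

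A simple difference in mean change sets the coefficient of the baseline value at 1. When the correlation between visits is below 1, the best coefficient (with equal standard deviations) is rho. Using 1 in its place adds avoidable variance and leaves any chance baseline imbalance incompletely corrected in the particular trial. Leaving out stratification factors that predict the outcome tends to overstate the standard error, because the variation they explain stays in the residual although the design has balanced it.

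What is at stake is power and the width of the confidence interval for the primary outcome, in a trial planned at about 80% power.

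**Working it through.** **Inputs from the article (Power Calculation, Randomization).** Difference 2 percentage points; two-sided 5%; power at least 80%; 280 families randomised 1:1; 80% retention.

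**Inputs not in the article (assumed ranges).** rho from 0.5 to 0.95; share of outcome variance explained by the strata (R-squared) from 0.01 to 0.10.

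**Step 1: the planned sample size.** Analysed families: 280 × 0.80 = 224, or 112 per arm. No standard deviation is given, so 280 cannot be reproduced independently. It can only be solved backwards:

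SD of change = 2 / [(1.960 + 0.842) × sqrt(2/112)] = 5.34 points.

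Putting 5.34 back returns 112 per arm and 280 randomised, which is circular. For scale, an SD of 5 would need 248 families and an SD of 6 would need 355.

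**Step 2: variance with and without baseline adjustment.** With SD sigma at both visits, the per-child variances are:

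- Change score: 2 sigma² (1 − rho)
- Baseline-adjusted: sigma² (1 − rho²)
- Ratio, adjusted to change: (1 + rho)/2

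**Step 3: effect on power.** At 80% power the expected z statistic is 1.960 + 0.842 = 2.80. Adjustment raises it to 2.80 / sqrt(ratio), and power = Phi(2.80 / sqrt(ratio) − 1.96). This uses only the stated 80% and the ratio, so the missing SD does not matter here.

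| Assumed rho | Variance ratio | Power at 224 analysed | Difference detectable at 80% power, 2 × sqrt(ratio) | Randomised N for 80% power |
|---|---|---|---|---|
| 0.5 | 0.75 | 89.9% | 1.73 | 210 |
| 0.7 | 0.85 | 86.0% | 1.84 | 240 |
| 0.9 | 0.95 | 82.0% | 1.95 | 268 |
| 0.95 | 0.975 | 81.0% | 1.97 | 275 |

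**Step 4: strata.** Adjusting for the strata alone multiplies the residual variance by (1 − R-squared). Power goes from 80% to 80.4%, 82.0% or 84.0% at assumed R-squared of 0.01, 0.05 or 0.10. This is not simply additive with step 3, because strata and baseline may explain the same variation.

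**Step 5: what the planning figures suggest about rho.** SD of change = sigma × sqrt(2(1 − rho)). With 5.34 from step 1, sigma would be 5.3 at rho 0.5, 6.9 at 0.7 and 11.9 at 0.9. A very high rho therefore fits the planned sample size only if percent body fat varies widely between children. This is indirect evidence, and it assumes that 280 contains no allowance beyond dropout.

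**Step 6: adjusting does not change the estimand.** Take change = a + b × arm + c × baseline. Adding baseline to both sides gives follow-up = a + b × arm + (1 + c) × baseline. The arm coefficient b is the same in both.

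**The case against.** The strongest objection is that this is silence, not error. The article is a condensed account. It names no test or model, and covariates are normally set out in a full protocol or analysis plan that is not at hand. A difference in mean change is a legitimate target and can be estimated from an adjusted model. That stands. A reader might infer that the trial will compare raw changes and ignore its strata, but nothing in the text says so. What remains is that the article states the contrast and the stratification explicitly and does not connect them.

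A reader might also infer that the 20% of families expected to be lost (280 × 0.20 = 56) will be dropped. The text does not support this. The phrase "a retention rate of 80% at the post-intervention assessment" is a sample-size assumption, and the Evaluation section gives no rule for missing outcomes. Nor would baseline adjustment alone address it, because a regression of the 35-week value on baseline needs that value just as a change score does.

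The gain may be small. The body fat formula also uses weight, sex and race/ethnicity, and the last two do not change between visits, so a high rho is plausible. At 0.95 the gain is one power point. Against this, triceps skinfold is read only to the nearest 1.0 mm. The documents do not settle the value.

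Finally, cards are shuffled in pails and leftovers carry over between events. The blocks of 2 are thus not kept in sequence, and balance within strata is approximate. This weakens the argument that omitting strata overstates the standard error, but not the case for conditioning on them.

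**Conclusion.** The point holds as one of precision. The article defines the primary comparison as a difference in mean change and names no adjustment for baseline percent body fat, income, county or wave. If analysed that way without covariates, the result would be valid under randomisation, so a reading that the primary estimate is biased is not supported.

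The loss relative to baseline adjustment is between about 1 and 10 power points for rho from 0.95 down to 0.5, with strata adding a little more. These figures assume equal standard deviations at both visits, a nominal 80% power for the unadjusted comparison and 224 analysed families. Because rho is assumed, the size is a range and not an estimate. The change is worth making because it is nearly free.

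**What to change.** Check whether the full protocol or analysis plan already specifies adjustment. If it does not, add the following before any outcome data are examined by arm.

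- **Estimand:** keep the between-arm difference in change in child percent body fat at 35 weeks.
- **Model:** linear regression on arm, baseline percent body fat, income stratum, county and wave. Either change or the 35-week value may be the outcome, since the treatment effect is the same. Main effects are the simplest choice for the stratification factors, as the article does not state the number of counties and some combined cells may be small.
- **Optional extension:** a longitudinal model with baseline kept in the outcome vector, so that families without a 35-week visit contribute the measurements they have. It differs from the regression in this respect and relies on outcomes being missing at random given the observed data.

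The cost is analysis wording only. Baseline percent body fat is measured before randomisation, and income stratum, county and wave are already recorded in order to randomise. The sample size need not change.

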## Discussion

The Parenting SOS program offers an innovative approach to addressing healthy weight development in families with preschool-age children. The intervention is based on considerable formative and pilot research, and addresses general parenting as the gateway activity for parents to develop appropriate parenting skills for their children's healthy eating and activity patterns. Responding to our formative data, we developed a companion child program that offers our families support in making changes to current lifestyle practices. In addition to the innovative intervention content, the Parenting SOS program is theory-driven based on Self-Determination and Social Cognitive theories.

Because of the pioneering nature of this study, we include numerous measures of the social, environmental, and behavioral components of family life in anticipation to increase our understanding of the factors that moderate and mediate healthy weight parenting behaviors and, ultimately, child body fat development.
